| Feasibility counts Feasibility counts presented below are based on the January 2018 version of the CPRD GOLD primary care database.  We identified 65,136 women who had a diagnosis of breast cancer (Read codes provided in appendix 2) while aged between 18 and 80 years, registered with a primary care practice contributing with data to CPRD, and whose individual records were acceptable for research. Non-interrupted one year of follow up before the cancer diagnosis (index date) was not available for 6,757 women, and 6,044 women were further excluded because they had a lifetime diagnosis of severe mental illness or another cancer before their breast cancer diagnosis (see section J for the inclusion and exclusion criteria).  Hence, 52,335 women with a history of breast cancer were identified as eligible for this study; the table below provides details of the distribution by age and calendar period of diagnosis.  Table 1 Distribution of women with breast cancer history who are eligible for this study, by age and calendar period of diagnosis.   \|  \| **N** \| **%** \| \| --- \| --- \| --- \| \|  \|  \|  \| \| **All study participants** \| **52,335** \| **(100.0)** \| \|  \|  \|  \| \| **Calendar period of diagnosis** \|  \|  \| \| 1989-1994 \| 3,184 \| (6.1) \| \| 1995-1999 \| 4,768 \| (9.1) \| \| 2000-2004 \| 10,934 \| (20.9) \| \| 2005-2009 \| 14,705 \| (28.1) \| \| 2010-2014 \| 13,805 \| (26.4) \| \| ≥2015 \| 4,939 \| (9.4) \| \|  \|  \|  \| \| **Age at diagnosis (years)** \|  \|  \| \| 18-24 \| 24 \| (0.1) \| \| 25-34 \| 771 \| (1.5) \| \| 35-44 \| 4,916 \| (9.4) \| \| 45-54 \| 12,235 \| (25.3) \| \| 55-64 \| 14,910 \| (28.5) \| \| 65-74 \| 12,811 \| (24.5) \| \| 75-80 \| 5,668 \| (10.8) \| \|  \|  \|  \|   A comparison group of women without cancer (4 controls per breast cancer case) will be randomly selected from the same data source, same primary care practice and within a 3-year age range.  Appendix 2 provides the list of Read codes used to identify women with a history of breast cancer in the CPRD GOLD primary care database. The list of Read codes used to identify cancer diagnoses other than the breast one (exclusion criterion) has been published elsewhere [14]. A provisional list of Read codes to identify women with several mental illnesses (exclusion criterion) was defined for the purpose of this calculation; the final list will be refined in due course. |

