| Sample size considerations Table 2 shows the minimum relative risk that could be detected with the 52,335 women identified in the CPRD GOLD primary care database, for different probabilities of type I (α) and type II error (β). These estimates were obtained with the command ‘power’ in Stata v15 [15].  Table 2 Minimum RR that can be detected with the 52,355 women with a history of breast cancer and 209,420 women who did not have cancer, for different probabilities of type I and type II errors, and baseline risk of the outcomes.   \| **Outcome** \| **α** \| **β** \| **% of outcome in unexposed group [ref]** \| **Min. HR possible to be estimated** \| \| **RR/HR estimated in other studies [ref]** \| \| \| --- \| --- \| --- \| --- \| --- \| --- \| --- \| --- \| \|  \|  \|  \|  \|  \| \|  \| \| \| **Primary outcomes** \|  \|  \|  \|  \| \|  \| \| \|  \|  \|  \|  \|  \| \|  \| \| \| **Anxiety, diagnoses** \| **0.05** \| **0.20** \| **5 [7]** \| **1.05** \| \| 1.06 [7]  1.08 [7]  1.22 [11]  1.25 [8] \| \| \| **0.01** \| **0.20** \| **5 [7]** \| **1.06** \| \| \| **0.05** \| **0.10** \| **5 [7]** \| **1.06** \| \| \| 0.01 \| 0.10 \| 5 [7] \| 1.07 \| \| \|  \|  \|  \|  \| \| \| **0.05** \| **0.20** \| **20 [11]** \| **1.02** \| \| \| **0.01** \| **0.20** \| **20 [11]** \| **1.03** \| \| \| **0.05** \| **0.10** \| **20 [11]** \| **1.03** \| \| \| **0.01** \| **0.10** \| **20 [11]** \| **1.03** \| \| \|  \|  \|  \|  \|  \| \|  \| \| \| **Anxiety, prescription of**  **anxiolytics** \| **0.05** \| **0.20** \| **3 [10]** \| **1.07** \| \| 1.08 [7]  2.52 [10] \| \| \| **0.01** \| **0.20** \| **3 [10]** \| **1.08** \| \| \| **0.05** \| **0.10** \| **3 [10]** \| **1.08** \| \| \| 0.01 \| 0.10 \| 3 [10] \| 1.09 \| \| \|  \|  \|  \|  \| \| \| **0.05** \| **0.20** \| **8 [7]** \| **1.04** \| \| \| **0.01** \| **0.20** \| **8 [7]** \| **1.05** \| \| \| **0.05** \| **0.10** \| **8 [7]** \| **1.05** \| \| \| **0.01** \| **0.10** \| **8 [7]** \| **1.06** \| \| \|  \|  \|  \|  \|  \| \|  \| \| \| **Depression, diagnoses** \| 0.05 \| 0.20 \| 3 [11] \| 1.07 \| \| 1.06 [7]  1.39 [9]  1.49 [8]  1.94 [11] \| \| \| 0.01 \| 0.20 \| 3 [11] \| 1.08 \| \| \| 0.05 \| 0.10 \| 3 [11] \| 1.08 \| \| \| 0.01 \| 0.10 \| 3 [11] \| 1.09 \| \| \|  \|  \|  \|  \| \| \| **0.05** \| **0.20** \| **9 [7]** \| **1.04** \| \| \| **0.01** \| **0.20** \| **9 [7]** \| **1.05** \| \| \| **0.05** \| **0.10** \| **9 [7]** \| **1.04** \| \| \| **0.01** \| **0.10** \| **9 [7]** \| **1.05** \| \| \|  \|  \|  \|  \|  \| \|  \| \| \| **Depression, prescription of**  **antidepressants** \| **0.05** \| **0.20** \| **2 [10]** \| **1.08** \| \| 1.16 [7]  1.95 [10] \| \| \| **0.01** \| **0.20** \| **2 [10]** \| **1.10** \| \| \| **0.05** \| **0.10** \| **2 [10]** \| **1.09** \| \| \| **0.01** \| **0.10** \| **2 [10]** \| **1.11** \| \| \|  \|  \|  \|  \| \| \| **0.05** \| **0.20** \| **20 [7]** \| **1.02** \| \| \| **0.01** \| **0.20** \| **20 [7]** \| **1.03** \| \| \| **0.05** \| **0.10** \| **20 [7]** \| **1.03** \| \| \| **0.01** \| **0.10** \| **20 [7]** \| **1.03** \| \| \|  \|  \|  \|  \|  \| \|  \| \| \| **Secondary outcomes *** \|  \|  \|  \|  \| \|  \| \| \|  \|  \|  \|  \|  \| \|  \| \| \| **Sexual dysfunction** \| 0.05 \| 0.20 \| 4.1 [16] \| 1.06 \| \| 1.03 [16]  2.27 [17] \| \| \| 0.01 \| 0.20 \| 4.1 [16] \| 1.07 \| \| \| 0.05 \| 0.10 \| 4.1 [16] \| 1.07 \| \| \| 0.01 \| 0.10 \| 4.1 [16] \| 1.08 \| \| \|  \|  \|  \|  \| \| \| 0.05 \| 0.20 \| 9.1 [17] \| 1.04 \| \| \| 0.01 \| 0.20 \| 9.1 [17] \| 1.05 \| \| \| 0.05 \| 0.10 \| 9.1 [17] \| 1.04 \| \| \| 0.01 \| 0.10 \| 9.1 [17] \| 1.05 \| \| \|  \|  \|  \|  \|  \| \|  \| \| \| **Suicide** \| 0.05 \| 0.20 \| 0.0008** [18] \| 1.47 \| \| 1.37 [18]  1.6 [19] \| \| \| 0.01 \| 0.20 \| 0.0008** [18] \| 1.60 \| \| \| 0.05 \| 0.10 \| 0.0008** [18] \| 1.57 \| \| \| 0.01 \| 0.10 \| 0.0008** [18] \| 1.70 \| \| \|  \|  \|  \|  \|  \| \|  \| \| \| **Fatal and**  **non-fatal self-harm** \| 0.05 \| 0.20 \| 0.005 [18, 20] \| 1.17 \| \| 1.03 [21]  1.37 [18] \| \| \| 0.01 \| 0.20 \| 0.005 [18, 20] \| 1.21 \| \| \| 0.05 \| 0.10 \| 0.005 [18, 20] \| 1.20 \| \| \| 0.01 \| 0.10 \| 0.005 [18, 20] \| 1.24 \| \| \|  \|  \|  \|  \|  \| \|  \| \| \| **Sleep disturbances** \| 0.05 \| 0.20 \| 50 [22] \| 1.01 \| \| 0.8 [22] \| \| \| 0.01 \| 0.20 \| 50 [22] \| 1.02 \| \| \| 0.05 \| 0.10 \| 50 [22] \| 1.02 \| \| \| 0.01 \| 0.10 \| 50 [22] \| 1.02 \| \| \|  \|  \|  \|  \|  \| \|  \| \| \| **Prescription of hypnotics** \| **0.05** \| **0.20** \| **4 [23]** \| **1.06** \| \| 3.75 [23] \| \| \| **0.01** \| **0.20** \| **4 [23]** \| **1.07** \| \| \| **0.05** \| **0.10** \| **4 [23]** \| **1.07** \| \| \| **0.01** \| **0.10** \| **4 [23]** \| **1.08** \| \| \|  \|  \|  \|  \|  \| \|  \| \| \| **Mild cognitive impairment** \| **0.05** \| **0.20** \| **5 [24]** \| **1.05** \| \| 1.58 [25]  1.60 [26]  2.43 [24]  3.67 [27] \| \| \| **0.01** \| **0.20** \| **5 [24]** \| **1.06** \| \| \| **0.05** \| **0.10** \| **5 [24]** \| **1.06** \| \| \| **0.01** \| **0.10** \| **5 [24]** \| **1.07** \| \| \|  \|  \|  \|  \| \| \| **0.05** \| **0.20** \| **19 [26]** \| **1.02** \| \| \| **0.01** \| **0.20** \| **19 [26]** \| **1.03** \| \| \| **0.05** \| **0.10** \| **19 [26]** \| **1.03** \| \| \| **0.01** \| **0.10** \| **19 [26]** \| **1.04** \| \| \|  \|  \|  \|  \| \|  \| \|  \| \|   HR – hazard ratio. RR – risk ratio. Bold is used to denote where the minimum risk ratio that could be detected with the available sample size is lower than the lowest estimate reported in the literature.  * No population-based studies have been identified reporting the relative risk of sexual dysfunctions, pain, fatigue, sleep disorders or cognitive dysfunction in breast cancer survivors compared to the non-cancer female population. Thus, the relative risk reported in the column for the other studies comes from studies involving convenience samples of cancer survivors. Pain and fatigue are often evaluated using psychometric instruments whose mean scores are summarised as means for between-group comparisons; no studies were identified providing data for the prevalence of pain and fatigue in breast cancer survivors and in women who did not have cancer, and thus these two outcomes were not included in the table.  ** Calculated as the proportion of suicides in the exposed group divided by the inverse of the standardised mortality ratio reported in the original study.  The available sample size is expected to be sufficient for detecting clinically significant increases of anxiety and depression (primary outcomes) in breast cancer survivors compared to the women who did not have cancer.  For the secondary outcomes, sample size is likely to be enough to assess differences in sleep disturbance measured by hypnotics’ prescription, and mild cognitive impairment. However, the available sample size will have relatively small power to detect small differences in suicide between women with history of breast cancer and those who did not have cancer, because this is a rare outcome, but we will still have enough power to detect associations of a magnitude seen in some previous studies; data from our analysis can also contribute to future meta-analyses. |

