| Planned use of linked data (if applicable): The following linkages will be requested:  Death registration data from the Office for National Statistics (ONS)  HES Admitted Patient Care (HES-APC)  Index of Multiple Deprivation 2015 (IMD), practice and patient level  Data coming from these data sets will supplement information available in the CPRD GOLD primary care database, but linked data will be used in sensitivity analysis only.  Data from the ONS-mortality and HES-APC databases will be important to increase the completeness and validity of some outcomes. For example, for suicide, only 26% of the suicides registered in the ONS mortality data (gold standard) were captured in CPRD, indicating low sensitivity of this source [28]. Similarly for non-fatal self-harm, only 68% of the cases registered in HES-APC could be identified in CPRD [28]. Of note, patients who had the outcome recorded in the year prior to the index date will be excluded, and thus this finer definition of the outcomes will impact patients’ selection and patients’ who are identified as having had the outcome. Information on the exposure will not be supplemented by data from HES-APC.  Patient-level quintiles of IMD will be used to control for socioeconomic status, which is a major confounder of the association between breast cancer history and adverse mental health outcomes. Even though women in the comparison group are selected from the same primary care practice of the index-case, and thus IMD at practice level will not vary by matched set, the patient-level IMD will allow for a finer adjustment of socioeconomic status. Practice level of IMD is requested to allow us to study effect modification in the full dataset.  We acknowledge that analyses including linked data will be restricted to the subset of practices and patients who consent to the linkage scheme (~75% of the practices in England); the coverage periods for the dataset will be taken into account (see table below). This will result in reductions in sample size and potentially impact the power of the study to reject the null-hypothesis. Thus, these data will be used in sensitivity analysis only.  Table 3 Coverage period of the data included in the databases that will be linked to the CPRD GOLD primary care database.   \| **Database** \| **Coverage period** \| \| --- \| --- \| \| HES Admitted Patient Care (APC) \| April 1997 – December 2017 \| \| ONS death registration \| January 1998 – February 2018 \| |

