| Exposures, Outcomes and CovariatesExposure: breast cancer Women will be considered exposed at the day of the breast cancer diagnosis (index date), denoted by the first entry of one or more of the Read codes provided in appendix 2. Primary outcomes: anxiety and depression To our knowledge, there is no validated list of Read codes to identify anxiety and depression in the CPRD GOLD primary care database. Algorithms will be developed and tested to identify anxiety and depression cases in CPRD. The algorithms will be chiefly determined by clinical diagnoses of anxiety and depression registered in the EHR with Read codes, and supplemented with information from drug prescriptions, referrals, and symptoms (if deemed suitable). Please see section N, plan of analysis for specific aim 1, for more details on the construction and validation of algorithms. Secondary outcomes: fatigue, mild cognitive impairment, pain, sleep disturbance, sexual dysfunction, and fatal and non-fatal self-harm Similarly, we will develop and test outcome-specific algorithms that identify events using a hierarchy of data on clinical diagnoses, prescriptions, referrals and symptoms.  In sensitivity analysis, we will consider linked data (see section J for data linkage requested) to develop more precise definitions of the outcomes, when possible. For example, two definitions of suicide will be considered: (1) considering Read codes only to identify suicides in CPRD; (2) considering Read codes for suicide as well as death registration data where suicide was recorded as primary cause of death (ICD-10 codes provided in appendix 3) Covariates Variables considered as potential confounders or effect modifiers of the association between breast cancer history and anxiety and depression (the primary outcomes of this study) are described below. The directed, acyclic graph (DAG) in appendix 4 explicitly describes the assumptions of the causal relations between the variables that underpin the choice. Please refer to the data analysis (section N) for details on which variables will be considered for sensitivity analyses only. *Potential confounders*  - Age at diagnosis (categorical variable, in 10-year age bands)   Defined as the absolute difference between the year of breast cancer diagnosis and year of birth. Age is a strong risk factor for breast cancer and for mental disorders.   - Alcohol drinking habits at diagnosis (categorical variable: current drinker, former drinker, never drinker)   Excess alcohol drinking is a well-established risk factor for breast cancer [30], besides being positively associated with anxiety and depression [31-33]. The most recent data on alcohol drinking habits prior to index date will be used in analysis. Current drinking will be further sub-divided into high, moderate, low or unknown intake of alcohol.   - Body mass index at diagnosis (categorical variable: underweight, normal weight, overweight, obesity class I, obesity class II and above)   Calculated as BMI=(weight/height^2^). Higher body mass index is protective against breast cancer in pre-menopausal women, but a risk factor for breast cancer post-menopause [34]. Obesity increases the risk of anxiety and depression [35, 36]. The most recent recording of BMI prior to index date will be used in analysis. The BMI values will be categorised into 5 categories: <18.5 kg/m^2^ (underweight), 18.5-24.9 kg/m^2^ (normal weight), 25.0-29.9 kg/m^2^ (overweight), 30.0-34.9 kg/m^2^ (obesity class I), ≥35.0 kg/m^2^ (obesity class II and above). Read codes for body weight categories recorded in the year prior to the breast cancer diagnosed will be considered to supplement missing information for this variable.   - Calendar period of diagnosis (categorical variable: ≤1994; 1995-1999; 2000-2004; 2005-2009; 2010-2014; >2014)   Even though calendar time *per se* does not change the risk of breast cancer, the risk of being diagnosed with breast cancer changed over time, probably due to increase awareness of the disease along with widespread use of mammography to screen for breast cancer. Time has also contributed for mental disorders being more likely to be diagnosed, due to raises awareness and increased recognition of the importance of mental disorders among health care professionals.   - Diabetes mellitus (dichotomous variable: yes/no)   Diabetes mellitus has been associated with an increased risk of breast cancer [37] and depression [38]. Algorithms previously defined elsewhere will be applied to identify patients with diabetes mellitus in the CPRD GOLD primary care database [39, 40].   - Level of deprivation (categorical variable: quintiles of patient-level IMD).   The IMD is an ecological measure of deprivation for small areas in England that combines information from seven domains (income, employment, education, health deprivation, crime, barriers to housing, and living environment), and ranks the small area from 1 (most deprived) to 32,844 (least deprived). Patients will be categorised in quintiles of IMD, with quintile 1 representing those least deprived and quintile 5 those most deprived.   - Menopausal status (dichotomous variable: premenopausal/postmenopausal)   Menopausal status is a potential confounder of the association between breast cancer history and depression, as the risk of breast cancer increases with menopause [30], and so does the risk of depression [42]. However, information on menopausal status is not easily available in the CPRD database. We will therefore produce results stratified by an age cut-off, as a proxy of the menopausal status of the women. The cut-off will be the mean/median age at natural menopause in the UK.   - Smoking history at diagnosis (categorical variable: current smoker, former smoker, never smoker)   Information on Read codes available on the data will be used to classify patients by smoking history. The most recent data on smoking prior to index date will be used in analysis. *Potential effect modifiers*  - Living alone (dichotomous variable: yes/no)   Ascertained from the CPRD GOLD primary care data using Read codes (list provided in [41]) and the patient’s family number (variable ‘famnum’ from the patient file). Women living in household of <2 people will be classified as living alone.   - Residing in a care home (dichotomous variable: yes/no).   This variable will be defined from the CPRD GOLD primary care database, using Read codes (list provided in [41]), and information gathered in the family number variable (‘famnum’). For the latter, ‘care home’ will be defined as a household with >3 individuals aged ≥65 years and if their total count was more than of individuals <65 years.   - Ethnicity (categorical variable: White, South Asian, Black, Others and mixed)   Ethnicity data recorded in the CPRD GOLD primary care database will be categorised in five groups, following the categories defined in the UK 2011 Census: White, South Asian, Black, Others and mixed. This variable will be derived from Read codes available in the CPRD GOLD primary care database and from HES, since the combined data sources increase completeness from 55% to 79% [41]. For analysis, four groups will be considered: White, South Asian, Black, Others and mixed.   - Previous mental health history (categorical variable: yes/no)   Mental health history will be defined as having had an episode of anxiety- or depression-related disorders (primary outcomes) or any the secondary outcomes, ever recorded at more than 1 year before the breast cancer diagnosis (patients who had the outcome in the year before the breast cancer diagnosis will be excluded from the cohort). These will be identified based on the algorithms defined in aim 1 of this study.   - History of stroke or coronary heart disease at diagnosis (two dichotomous variables: yes/no)   These will include ischaemic heart disease (angina and myocardial infarction) and stroke, which are amongst the leading causes of disability-adjusted life years in females in the UK. These will be identified through Read codes recorded in the CPRD GOLD primary care database.   - Socioeconomic status (IMD quintiles of deprivation)   The IMD is an ecological measure of deprivation for small areas in England (Lower Super Output Areas). It combines information from seven domain indices (income, employment, education, health deprivation, crime, barriers to housing, and living environment). The index ranks the areas from 1 to 32,844; usually the quintiles are used for research purposes: from 1 (most deprived) up to 5 (least deprived). The IMD is linked to the primary care data using the postcode of the patient or practice. *Potential mediators of the association between breast cancer history and anxiety/depression*  - Sequelae from cancer treatments (six separate binary variables (yes/no): lymphoedema, pain, mild cognitive impairment, fatigue, sexual dysfunction, sleep disorder)   Lymphoedema will be defined using Read codes for the condition, in the CPRD GOLD primary care database. Pain, mild cognitive impairment, fatigue, sexual dysfunction, and sleep disorder are secondary outcomes of this study, and will be identified based on the algorithms defined in aim 1 of this study. Patients will be classified as having had one of these conditions if there was more than one record for these conditions within a 6-month interval.   - Exposed to endocrine treatment for breast cancer: binary variable (yes/no).   This will be defined from the CPRD GOLD primary care database using Read codes for at least two prescriptions of anastrozole, tamoxifen, exemestane, or letrozole [43] within a 6-month period. |

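### The suicide power claim assumes full capture of suicides in the full cohort, but the main analysis relies on primary care records that capture about 26% of them

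*Protocol*

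**What the plan says.** The section on planned use of linked data calls ONS mortality the gold standard for suicide and reports that "only 26% of the suicides registered in the ONS mortality data (gold standard) were captured in CPRD, indicating low sensitivity of this source". It goes on to say that linkage restricts the analysis to a subset of practices and patients (about 75% of practices in England), which may cost power, and concludes: "Thus, these data will be used in sensitivity analysis only".

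The section on exposures, outcomes and covariates sets out two suicide definitions. The first is "1) considering Read codes only to identify suicides in CPRD". The second adds death registration, and linked definitions are placed under sensitivity analysis. The main suicide analysis therefore rests on primary care records alone.

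The sample size section gives suicide its own row in Table 2: baseline 0.0008, with minimum detectable ratios 1.47, 1.60, 1.57 and 1.70 for (alpha, beta) = (0.05, 0.20), (0.01, 0.20), (0.05, 0.10) and (0.01, 0.10). The cohort is given as "52,355 women with a history of breast cancer and 209,420 women who did not have cancer", and the literature effects listed are 1.37 and 1.6. A footnote derives the baseline from a standardised mortality ratio. The text concedes limited power for small differences because suicide is rare, but adds that "we will still have enough power to detect associations of a magnitude seen in some previous studies".

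**The concern.** For a rare event, power follows the number of events seen, not the number of women followed. The main analysis has the full cohort but about a quarter of the suicides; the linked analysis has the suicides but only part of the cohort. The Table 2 row describes neither, because it combines full capture with full size.

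Two things are at stake. A reader who relies on the power statement could take a null result from the main suicide analysis as evidence against an effect near 1.6, when that analysis would have about an even chance or less of detecting it. And the reason for demoting the linked definition, loss of power, may point the other way for this outcome.

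**Working it through.** **Inputs from the protocol**
- Women: 52,355 exposed and 209,420 unexposed (Table 2 title), 261,775 in all. The feasibility section gives 52,335 exposed; the difference does not change the results.
- Baseline suicide risk: 0.0008. It must be a proportion although the column is headed %. Read as a literal percentage, it would give a two-sided minimum RR of about 11.4.
- Capture of suicides in primary care records: 26%.
- Literature effects: 1.37 and 1.6.
- Software: the Stata power command. Neither the test nor its sidedness is stated.

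**Assumptions**
- The 26% holds for this study's suicide algorithm, which is still to be developed.
- The 0.0008 reflects full ascertainment of deaths (inferred from the mortality-ratio footnote).
- The linkable share within ONS coverage is 40–75% of the cohort. The protocol gives no such share.

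**Formula.** Two-proportion test with pooled variance under the null, p1 = RR × p0:

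power = Φ[ (p1 − p0 − z·s0) / s1 ]

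where s0 = √{p̄(1−p̄)(1/n1 + 1/n0)}, s1 = √{p1(1−p1)/n1 + p0(1−p0)/n0}, p̄ is the overall proportion, and z = 1.645 (one-sided) or 1.960 (two-sided) at alpha 0.05.

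**Step 1: reproduce the row.** One-sided with p0 = 0.0008 gives minimum RRs of 1.467, 1.602, 1.566 and 1.706, against the stated 1.47, 1.60, 1.57 and 1.70. The two-sided version gives 1.53, 1.65, 1.63 and 1.76. Two-sided log-RR, unpooled, Schoenfeld and Freedman calculations do not match the row either. So the row corresponds to full capture, the full cohort and, apparently, a one-sided test.

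**Step 2: apply the capture.** p0 = 0.0008 × 0.26 = 0.000208.
- Suicides expected with no effect: 0.0008 × 261,775 = 209; × 0.26 = 54.
- Worked case, RR 1.6, one-sided: p1 − p0 = 0.0001248, s0 = 0.00007457, s1 = 0.00008572. Then (0.0001248 − 1.645 × 0.00007457)/0.00008572 ≈ 0.025, so power = 51%.

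| alpha 0.05 | Full capture, one-sided | 26% capture, one-sided | Full capture, two-sided | 26% capture, two-sided |
|---|---|---|---|---|
| Minimum RR, 80% power | 1.47 | 1.99 | 1.53 | 2.13 |
| Power at RR 1.6 | 92% | 51% | 87.5% | 40% |
| Power at RR 1.37 | 65% | 30% | 54% | 21% |

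With 26% capture the minimum RR lies above both literature values, whichever sidedness is used.

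**Step 3: the linked definition.** With full capture in a fraction f of the cohort, expected suicides are 209 × f. This exceeds 54 once f is above about 26%.

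| Linked share f (assumed) | Suicides expected, no effect | Minimum RR, one-/two-sided | Power at RR 1.6, one-/two-sided |
|---|---|---|---|
| 40% | 84 | 1.78 / 1.88 | 65% / 54% |
| 50% | 105 | 1.68 / 1.78 | 72% / 62% |
| 75% | 157 | 1.55 / 1.62 | 85% / 78% |

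**Step 4: does the same hold for the self-harm composite?** Suppose its 0.005 splits into 0.0008 fatal and 0.0042 non-fatal (assumption), with primary care capture of 26% and 68%.
- Full cohort, primary care records: (0.000208 + 0.002856) × 261,775 ≈ 802 events.
- ONS for the fatal part, primary care records for the rest, in 50–75% of the cohort: (0.0008 + 0.002856) × 261,775 × f ≈ 479–718 events.

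Break-even is 0.003064/0.003656 ≈ 84% linked, so the argument does not carry over to the composite.

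**The case against.** The protocol is open about most of this. It states the 26%, requests the linkage to improve completeness, writes down the linked definition and matches on linkage eligibility. It concedes limited power for small differences, and no suicide row is in bold, so it does not claim to detect 1.37. Suicide is secondary, and both analyses will be run. All of that stands, and it limits the severity. It does not repair the row or the power sentence: the concession is attributed to rarity alone, and the 26% never enters Table 2.

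The upper end of the linked range is also fairly called optimistic. The 75% in the protocol refers to practices in England, ONS coverage starts in January 1998, and Table 1 includes diagnoses from 1989. The usable share may therefore sit lower in the range, though the advantage on events persists down to about 26%.

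A reader might go further in four ways that the documents do not support:
- *That the study has no power for suicide.* It has 40–51% at RR 1.6.
- *That the whole gap between 1.47 and 2.13 is due to capture.* Part is sidedness: the like-for-like changes are 1.47 to 1.99 and 1.53 to 2.13.
- *That the suicide ratio will be biased.* Under-recording that is equal in both groups, without false positives, costs power. Bias would need recording to differ between them, on which the protocol is silent.
- *That the self-harm composite should move to linked data too.* Under the split above, that would lose events.

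**Conclusion.** The concern holds for completed suicide. The Table 2 suicide row and the accompanying power statement describe an analysis that is not planned. In the main analysis as written, power at RR 1.6 is roughly half of what the row implies, and neither literature effect is detectable at 80% power. The power reason for keeping linked data secondary is reversed for this outcome provided the linkable share exceeds about 26% of the cohort.

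This rests on the three assumptions listed with the inputs. The primary outcomes are unaffected, and the composite is little affected: applying 68% capture, a figure the protocol gives for non-fatal self-harm only, moves its two-sided minimum RR from 1.20 to about 1.25. Severity: should-fix.

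**What to change.** For completed suicide only:
1. Make the second definition (Read codes plus ONS death registration), in linkage-eligible women and within the ONS coverage window, the main analysis.
2. Keep Read codes alone in the full cohort as the sensitivity analysis.
3. Restate the Table 2 suicide row and the power sentence for the linked population, giving the actual linkable count, the test and its sidedness.

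At minimum, apply the 26% to the existing row and withdraw the claim of enough power. Leave the fatal and non-fatal self-harm composite and all other outcomes as planned.

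The cost is wording and one recalculation, since the linkage is already requested, matching already considers linkage eligibility and the definition is already written. The downside is narrower scope: the suicide result would apply to linked English practices from 1998 onward.
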